#### **4.2.2 Efficacy Evaluation (Phase II)**

**Note this section differs from the AGILE Master Protocol.**

Once the recommended phase II dose has been identified, phase II will start. In the first stage (Phase IIa) 66 patients are randomised between IV Favipiravir and placebo in a 1:1 allocation ratio. If the probability of the treatment effect (in terms of the viral load on Day 3) for the experimental arm being below 0 (i.e. in favour of IV Favipiravir) is more than 0.94, the study will stop for efficacy; if this probability is less than 0.3, then the study will stop for futility. Within this range, the trial will be expanded to stage 2 (Phase IIb) where an additional 132 patients are equally randomised between IV Favipiravir and placebo. Safety will be reviewed by a DMEC at regular intervals.

##### **4.2.2.1 Data monitoring ethics committee (DMEC)**

Refer to section 14.3 of the AGILE Master Protocol for definitions.

A DMEC will review results during the phase II stage evaluating safety and efficacy. Following each review, decision will be made to either:

- Stop evaluation due to high risk of harm
- Stop evaluation due to a low probability of IV Favipiravir having a meaningful effect
- Continue study
- Recommend IV Favipiravir for further evaluation in a definitive trial

There will be an interim analysis for harm and futility in phase II after 66 participants have been enrolled.

#### **Stopping criteria for harm or futility**

As per the master protocol, recruitment will cease if the probability that the risk of toxicity is at least 30% more than the control arm is 25% or more during phase I. Harm is defined by unacceptable toxicity as given by the Common Terminology Criteria for Adverse Events (CTCAE) criteria (see master protocol). Futility will be determined during phase II if after the initial 66 patients there is a less than 0.3 probability that the treatment effect is below 0.

#### **Stopping criteria for efficacy**

Efficacy will be established during phase II if after the initial 66 patients there is a greater than 0.94 probability that the change from baseline to Day 3 in viral load between arms is less than 0. The same criteria will also be used at the final analysis after 198 patients if the trial continues.

### **4.3 JUSTIFICATION FOR DOSE**

The starting dose of IV Favipiravir administered in the protocol is lower than doses delivered in the oral formulation in extensive previous clinical trials.

A twice daily dose of 600mg over 1 hour infusion is proposed as the starting dose of the first-in-human study. Once the safety and pharmacokinetics of the starting dose is understood, the dose and

frequency will be escalated to find an optimized regimen for the treatment of COVID-19 patients. The justification for the starting dose is provided in the following paragraphs:

#### *Justification of the Starting Dose*

The safety of a single oral dose of favipiravir was studied up to 2400mg (BID) in healthy Japanese adults as a part of the QT study (#JP115), and the safety of a repeated oral dose up to 1800/800 mg twice a day for 22 days was investigated in a repeated dose safety study with healthy Japanese adults (#JP120). The Cmax (mean ± SD) observed in these studies were 116.11 ± 20.39 and 106.41 ± 22.67 µg/mL (Day 12 of administration), and the highest Cmax observed in these studies were 155 and 140 µg/mL, respectively. Two adverse events were observed in these studies; one event of nasopharyngitis in the single dose study subject, and one event of upper abdominal pain and increased blood uric acid in the repeated dose study. None of these were serious.

The oral and intravenous administration routes were compared in cynomolgus monkeys in a repeated dose safety study at 150 mg/kg twice daily (#SBL063-073). The Cmax (mean ± SD) after the first dose were 71.5 ± 29.4 µg/mL (oral) and 286±27 µg/mL (intravenous), indicating the Cmax after intravenous administration could be 4 times higher than that of oral route.

A Phase I, randomized, double-blind, placebo-controlled, single ascending-dose study to evaluate the pharmacokinetics, safety and tolerability of Injectable Favipiravir in healthy subjects in Japan was completed in 2021. Eight subjects in 5 cohorts (300, 600, 1200, 1800, 2400 mg) received active drug and two received placebo intravenously. At 300 to 2400 mg doses of favipiravir, the geometric mean Cmax ranged from 13.20 to 125.94 µg/mL (SD 8.8 µg/mL), with a mean t1/2 of 1.5 hours at 300 mg, and 7.3 hours at the dose of 2400 mg.

No SAEs occurred in subjects who received favipiravir at doses of 300 to 2400 mg. Moderate adverse events occurred in 12.5% (1/8 subjects, 1 event of conjunctivitis) for 2400 mg favipiravir; however, this event was considered to be unrelated to favipiravir. All the other adverse events (n=8) were mild in severity. Of these, blood uric acid increased (1 event) and pyuria (1 event) were considered to be related to favipiravir. The Cmax after a single dose of 600 mg (60-minute infusion) in humans was a geometric mean of 8µg/mL, and including an empirical safety margin of 40% is well under the concentrations observed in higher doses given in #JP115 and #JP120 studies. In combination with the safety data generated from the IV formulation SAD study in healthy volunteers (300mg - 2400mg dose cohorts), a 600mg BID via intravenous infusion was proposed as the starting dose.

Dose escalation will be guided by safety data from the previous cohorts, with the magnitude of dose escalation being no more than a doubling from the previously tested dose. Doses were selected on the basis that our pharmacometric assessment (see figure above) indicated that doses ≥1200mg BID maintenance are expected to be required to maintain intracellular RTP metabolite concentration above its Km for the SARS-CoV-2 polymerase (Pertinez H., 2021).

#### **4.4 DEFINITION OF END OF TRIAL**

Refer to AGILE Master Protocol section 4.4

## **5 SELECTION AND ENROLMENT OF PATIENTS**

This section is in addition to the AGILE Master Protocol

## 5.1 INCLUSION CRITERIA

The main trial (Phase I and II) inclusion criteria are outlined in the AGILE Master Protocol and listed below.

1. Adult in-patients ( $\geq 18$  years) with laboratory confirmed COVID-19 infection by positive polymerase chain reaction (PCR) test within 7 days of randomisation
2. Ability to provide informed consent signed by study patient or legally acceptable representative
3. Women of childbearing potential (WOCBP) and male patients who are sexually active with WOCBP must agree to use a highly effective method of contraception (as outlined in section 5.4 below) from the first administration of trial treatment, throughout trial treatment and for the duration outlined in the candidate-specific trial protocol as well as addition 14 days for women and 7 days for men after the last dose of trial treatment.

Additional criteria specific to this candidate are:

4. Group A and B (moderate to severe disease). Patients with clinical status of Grades 4 (hospitalised, no oxygen therapy), 5 (hospitalised, oxygen by mask or nasal prongs), 6 (hospitalised, on non-invasive ventilation, or high flow oxygen) as defined by the WHO Clinical Progression Scale (WHO, 2020).
5. Less than or equal to 14 days from onset of COVID-19 symptoms

## 5.2 EXCLUSION CRITERIA

The main trial exclusion criteria are outlined in the master protocol as:

1. Alanine aminotransferase (ALT) and/or aspartate aminotransferase (AST)  $> 5$  times the upper limit of normal (ULN)
2. Stage 4 severe chronic kidney disease or requiring dialysis (i.e., estimated glomerular filtration (eGFR) rate  $< 30$  mL/min/1.73 m^2)
3. Pregnant or breast feeding
4. Anticipated transfer to another hospital which is not a study site within 72 hours
5. Known Allergy to any study medication
6. Patients taking the following prohibited drugs within 30 days or 5 times the half-life (whichever is longer) of enrolment:

There are no known prohibited drugs with Favipiravir.

The following drugs should be used with caution when given with Favipiravir (Liverpool, n.d.):

- Pyrazinamide: Pyrazinamide administration with favipiravir examined possible renal urate transporter interactions. Pyrazinamide increased blood uric acid levels 2 to 9 mg/dL over baseline. The addition of favipiravir increased blood uric acid levels 4 to 11 mg/dL over baseline, indicating a moderate additive effect.
- Repaglinide: Favipiravir administration with repaglinide, an anti-diabetic agent that is extensively metabolized by CYP2C8 and CYP3A4, increased repaglinide plasma AUC 30 to 50% due to inhibition of CYP2C8.

- Theophylline: Theophylline administration with favipiravir increases plasma Cmax and AUC of favipiravir through xanthine oxidase (XO) interaction. The primary metabolite of theophylline is known to be metabolized by XO which is partially involved in metabolism of favipiravir.
  - Famciclovir, Sulindac: Famciclovir and Sulindac are converted to active metabolite by Aldehyde Oxidase (AO). Favipiravir inhibits AO and decrease the concentration of active metabolite of Famciclovir and Sulindac.
  - Paracetamol: Coadministration of paracetamol (650 mg once daily) and favipiravir (1200 mg twice daily or 800 mg twice daily) increased paracetamol Cmax and AUC by 3% and 16% (1200 mg doses) and by 8% and 14% (800 mg doses). The daily dose of paracetamol in adults should be no more than 3000 mg/day (rather than 4000 mg/day).
7. Patients participating in another clinical trial of an investigational medicinal product (CTIMP) and actively taking CTIMP within 30 days

### 5.3 SCREEN FAILURES

Refer to AGILE Master Protocol section 5.4

### 5.4 CONTRACEPTION

Refer to AGILE Master protocol section 5.5, with the following amendments:

- Women of childbearing potential (WOCBP) and male patients who are sexually active with WOCBP must agree to use a highly effective method of contraception from the first administration of trial treatment, throughout trial treatment and an additional 14 days for women and 7 days for men after the last dose of trial treatment
- Abstinence would be considered acceptable during the inpatient stay and post discharge; and while transitioning to a highly effective contraceptive measure after leaving the unit. A transition plan to include contraception measures required until the new method becomes effective should be agreed prior to hospital discharge.

### 5.5 REGISTRATION / RANDOMISATION PROCEDURES

Patients are registered on the trial database following consent. Randomisation is performed within the trial database when patients have completed screening and eligibility has been confirmed.

## 6 TREATMENTS

IV Favipiravir and placebo are considered investigational medicinal products for the purpose of this protocol. Favipiravir will be provided free of charge by Fujifilm Toyama Chemical Co., Ltd. for patients recruited to the trial. Saline placebo (for phase II) will be provided by the clinical site.

### 6.1 TREATMENT SCHEDULE

Participants will receive IV infusions of Favipiravir or standard of care (Phase I) or saline placebo (Phase II) twice daily up to 7 days whilst hospitalised.

N.B. placebo only in phase II

|                  |                          |                                       |
|------------------|--------------------------|---------------------------------------|
| Arm Name         | IV Favipiravir           | Placebo                               |
| Type             | Small molecule antiviral | Placebo                               |
| Dose Formulation | Lyophilised              | Sterile 0.9% sodium chloride solution |

|                                       |                                                                                                                                                                       |                                                                                                                                                                       |
|---------------------------------------|-----------------------------------------------------------------------------------------------------------------------------------------------------------------------|-----------------------------------------------------------------------------------------------------------------------------------------------------------------------|
| Unit Dose Strength                    | 600mg/vial                                                                                                                                                            | Not applicable                                                                                                                                                        |
| Dosage Level(s)                       | (300 only if dose de-escalated) 600, 1200, 1800, 2400 mg BID (maximum)                                                                                                | Same volume as active IMP                                                                                                                                             |
| Route of Administration               | Intravenous Infusion                                                                                                                                                  | Intravenous Infusion                                                                                                                                                  |
| Dosing instructions                   | Deliver over 1 hour
Twice daily (every 12 hours (as per AGILE CST6 Acceptable Time Windows Working Instruction and protocol section 6.4)) for 7 days as inpatient. | Deliver over 1 hour
Twice daily (every 12 hours (as per AGILE CST6 Acceptable Time Windows Working Instruction and protocol section 6.4) ) for 7 days as inpatient |
| Packaging and Labelling               | IMP will be provided in a single-use vial in an individual carton and labelled as required per country requirements.                                                  | Not applicable.                                                                                                                                                       |
| Current/Former Name(s) or Aliases(es) | T-705                                                                                                                                                                 | Not applicable                                                                                                                                                        |

## 6.2 IMP SUPPLY

Favipiravir will be provided to participating sites for clinical trial use. Refer to the Pharmacy Manual and the Favipiravir Site Dosing Instructions for details on supply, storage and preparation. Placebo will be sourced locally.

## 6.3 PRODUCT HANDLING, STORAGE AND STABILITY

The storage condition of the IMP should be stored in upright position and protected from light at room temperature.

The investigator or designee must confirm appropriate temperature conditions have been maintained during transit for all study intervention received and any discrepancies are reported and resolved before use of the study intervention.

Under normal conditions of handling and administration, study intervention is not expected to pose significant safety risks to site staff. Take adequate precautions to avoid direct eye or skin contact and the generation of aerosols or mists.

For further information please refer to the pharmacy manual.

## 6.4 PREPARATION AND ADMINISTRATION

Please refer to the Pharmacy manual for more detailed information.

If patients miss a dose; record as missed dose if delayed by longer than four hours, and administer when next due. If able to administer within four hours, take as soon as able within that time and

record the actual time of dosing. If longer than four hours the dose is omitted, record missing dose administration.

## **6.5 ACCOUNTABILITY**

Drug accountability logs will be provided to sites who will be responsible for maintaining records during the study as follows:

- Amount of study medication received
- Amount distributed to each patient
- Amount of unused drug returned or destroyed at the Sponsors request

In the event of necessary disposal of opened but wasted medication, the disposal should be documented appropriately (i.e. witnessed), in accordance with applicable local regulations, and GCP procedures. Copies of all completed drug accountability logs will be returned to CRO for compliance checks.

## **6.6 STUDY INTERVENTION COMPLIANCE**

Participants will receive IMP or placebo (Phase II) directly from the investigator or delegated member of the clinical study team, under medical supervision. The date and start and stop times of the dose administered will be recorded in the source documents.

## **6.7 DOSE MODIFICATION**

See Section 6.4 for instructions if dose is delayed beyond stipulated Treatment Schedule (section 6.1).

See Section 7 for instructions to discontinue study treatment for safety reasons.

## **6.8 CONTINUED ACCESS TO STUDY INTERVENTION AFTER THE END OF THE STUDY**

COVID-19 is an acute illness and participants are not expected to need continued access to Favipiravir after the end of the study.

## **6.9 TREATMENT OF OVERDOSE**

No specific treatment is recommended for an overdose. The treating physician will manage participants symptoms as clinically indicated.

In the event of an overdose, the treating physician should:

1. Contact the CRO and the Chief Investigator(s) immediately.
2. Closely monitor the participant for AE/SAE and laboratory abnormalities.
3. Document the quantity of the excess dose as well as the duration of the overdosing in the eCRF.

## **6.10 CONCOMITANT MEDICATIONS**

Information on any medication received by the participant, including frequency and therapeutic indication from 30 days prior to randomisation and until Day 29 will be recorded in the electronic case report form (eCRF).

The Chief Investigator(s) should be contacted if there are any questions regarding concomitant or prior therapy.

## **6.11 PROHIBITED AND RESTRICTED THERAPIES DURING THE TRIAL**

There are no known prohibited drugs with Favipiravir.

The following drugs should be used with caution when given with Favipiravir (Liverpool, n.d.):

- Pyrazinamide: Pyrazinamide administration with favipiravir examined possible renal urate transporter interactions. Pyrazinamide increased blood uric acid levels 2 to 9 mg/dL over

baseline. The addition of favipiravir increased blood uric acid levels 4 to 11 mg/dL over baseline, indicating a moderate additive effect.

- Repaglinide: Favipiravir administration with repaglinide, an anti-diabetic agent that is extensively metabolized by CYP2C8 and CYP3A4, increased repaglinide plasma AUC 30 to 50% due to inhibition of CYP2C8.
- Theophylline: Theophylline administration with favipiravir increases plasma Cmax and AUC of favipiravir through xanthine oxidase (XO) interaction. The primary metabolite of theophylline is known to be metabolized by XO which is partially involved in metabolism of favipiravir.
- Famciclovir, Sulindac: Famciclovir and Sulindac are converted to active metabolite by Aldehyde Oxidase (AO). Favipiravir inhibits AO and decrease the concentration of active metabolite of Famciclovir and Sulindac.
- Paracetamol: Coadministration of paracetamol (650 mg once daily) and favipiravir (1200 mg twice daily or 800 mg twice daily) increased paracetamol Cmax and AUC by 3% and 16% (1200 mg doses) and by 8% and 14% (800 mg doses). The daily dose of paracetamol in adults should be no more than 3000 mg/day (rather than 4000 mg/day).

#### **6.12 PERMITTED CONCOMITANT MEDICATIONS**

All medication that the participant is receiving as local, established standard of care for acute COVID-19 is permitted, as are stable concomitant medications that are being administered for past medical history. Any concerns regarding the acceptability of potential treatments should be discussed with the Chief Investigator(s).

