| Phase:                  | Seamless Phase I/II                                                                                                                                                                                                                                                                                                                                                                                                                                                                                                                                                                                                                                                                                                                                                                                                                                                                                           |
| Population:             | 
Adult in-patients (≥18 years) with laboratory confirmed COVID-19 infection by positive polymerase chain reaction (PCR) test. We will include patients defined according to the WHO Clinical Progression Scale (WHO, 2020) as follows:
 
Group A and B (moderate to severe disease) – N.B. only Grades 4, 5 & 6 as defined by master protocol
 
 
Patients with clinical status of Grade 4 (hospitalised, no oxygen therapy), Grade 5 (hospitalised, oxygen by mask or nasal prongs) and Grade 6 (hospitalised, non-invasive ventilation or high flow oxygen)
 
                                                                                                                                                                                                                                                                             |

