Dexamethasone and IL-6 inhibitors such as Tocilizumab have been shown by large phase III platform clinical trials to improve outcomes in hospitalised patients with severe COVID-19 (requiring supplemental oxygen) and have become standard of care in many countries as recommended by WHO. A number of antiviral therapeutics are also recommended for use by WHO in non-severe COVID-19 including Paxlovid (Nirmatrelvir/ritonavir), Molnupiravir and Remdesivir (WHO, 2022). Many monoclonal antibody therapeutics, evaluated in large platform trials and given approval for use, have in many settings now been withdrawn due to a lack of efficacy against new variants.

There remains an important medical need for anti-viral therapeutics for the treatment of COVID-19. Antiviral treatment of severe disease in hospitalised patients may prevent progression to more severe sequelae of COVID-19 including respiratory failure, and non-respiratory complications of COVID-19 including thromboembolic disease leading to pulmonary embolism and stroke, arrhythmias, and shock, among others (Klok, 2020) (Chen, 2020). It may also reduce length of stay in overwhelmed treatment facilities and furthermore, antiviral treatment could potentially reduce risk of nosocomial transmission. Early anti-viral treatment of non-severe COVID-19 may reduce the risk of progression to severe disease and hospitalisation in patients at high risk either due to co-morbidity or immunocompromise (Gottlieb, 2022).

Favipiravir (6-fluoro-3-hydroxypyrazine-2-carboxamide; T-705) has been shown to be an antiviral drug with broad spectrum capabilities in non-clinical studies and has been investigated in clinical studies for its efficacy in uncomplicated influenza in adult patients. Favipiravir has also been employed in the treatment of Ebola in a clinical trial sponsored by the French Government in Guinea during the 2014

epidemic, where favipiravir showed suggestions of efficacy. Additional indications under consideration or used under compassionate use include severe fever with thrombocytopenia virus, rabies, Lassa fever, Jamestown Canyon virus and norovirus (Furuta, 2017).

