## **10 STATISTICS AND DATA ANALYSES**

### **10.1 METHOD OF RANDOMISATION**

**Note this differs from the AGILE Master Protocol and is the method of randomisation to be used for this specific candidate.**

For phase I, participants will be randomised 2:1 to IV Favipiravir or SoC.

For phase II, participants will be randomised in a 1:1 ratio to IV Favipiravir or placebo.

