## **Analysis**

Patients will be analysed according to the treatment to which they were randomised (efficacy population). In addition, a supplementary analysis of the primary endpoint will be conducted in all patients for whom there were no major protocol deviations that could impact treatment efficacy (to be defined in the statistical analysis plan).

The primary efficacy endpoint in phase II of the SARS-CoV-2 viral load (in log10) will be analysed using a Bayesian repeated measures model including all post-randomisation assessments up to and including Day 3. The model will adjust for treatment, baseline viral load, visit timepoint and interaction of treatment by visit, with a subject-specific random-effect and unstructured variance-covariance matrix. A non-informative (vague) prior will be used for all model parameters. Viral load data will be log10-transformed prior to analysis with treatment differences expressed on the log10 scale. If 94% of the posterior distribution of the treatment effect is below 0 (i.e. in favour of Favipiravir), the study will conclude the treatment is efficacious, at the interim or the final analysis.

For any deaths in the trial, the change in viral load will be assumed to be zero from the last measured timepoint. To assess the impact of missingness in the primary analysis due to missing data that are not missing at random (including death) sensitivity analyses will be performed. Details will be provided in the statistical analysis plan.

Once the last participant recruited completes the Day 29 assessment the data will be unblinded to allow a primary readout of this endpoint. Participants will continue to complete the remaining scheduled assessments and will not be unblinded at an individual level.

Further details on analysis methods for other endpoints will be detailed in a detailed SAP, which will be finalised and signed off prior to database lock.

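### The Phase II primary model for viral load leaves out antiviral use at randomisation, a likely prognostic factor that the protocol permits and already records

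*Protocol*

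**What the plan says.** Section 6.12 of the protocol says: "All medication that the participant is receiving as local, established standard of care for acute COVID-19 is permitted". Section 6.11 says: "There are no known prohibited drugs with Favipiravir". In Section 5.2 the only related exclusion is recent use of another investigational product.

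Section 2.1 notes: "A number of antiviral therapeutics are also recommended for use by WHO in non-severe COVID-19 including Paxlovid (Nirmatrelvir/ritonavir), Molnupiravir and Remdesivir". It describes severe disease as disease that needs supplemental oxygen. The synopsis (1.1) and Section 5.1 admit "Patients with clinical status of Grade 4 (hospitalised, no oxygen therapy") alongside Grades 5 and 6, so the trial enrols patients who count as non-severe on Section 2.1's own description.

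The Phase II primary endpoint (Section 3.2) is change in SARS-CoV-2 viral load from baseline to Day 3. For its analysis, Section 10.3.2 says: "The model will adjust for treatment, baseline viral load, visit timepoint and interaction of treatment by visit", with a subject random effect. On allocation, Section 10.1 says: "For phase II, participants will be randomised in a 1:1 ratio to IV Favipiravir or placebo". It names no stratification factor, and it says that it replaces the master protocol's method.

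The data needed are already collected. Section 6.10 has the eCRF record "Information on any medication received by the participant, including frequency and therapeutic indication from 30 days prior to randomisation and until Day 29".

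**The concern.** The endpoint is purely virological, and the permitted background drugs act on the same quantity over the same two days. Antiviral use at randomisation is therefore likely to predict the outcome. The protocol records it but uses it neither in allocation nor in the primary model.

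The covariate list is not left to the SAP. Section 10.3.2 defers the definition of major deviations, the detail of the missing-data sensitivity analyses and the methods for other endpoints, but it writes out the primary model itself.

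Three things are at stake. First, a chance imbalance in antiviral use would pass into the estimate uncorrected. This matters most at the 66-patient look, where only 33 patients per arm support a decision to stop. Second, some precision is given up for nothing. Third, after a null or futility result, nothing stated in the protocol would help a reader judge whether favipiravir had little effect or had little to add in patients already on an antiviral.

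**Working it through.** **1. The plan's own figures.** Inputs from Sections 10.2 and 10.3.2: 33 per arm at the interim and 99 per arm at the end; SD 1.5 log10; efficacy if the posterior probability exceeds 0.94 (both looks); futility if it is below 0.3 (interim). With a vague prior, the posterior probability is Φ(Z). The boundaries are then Z > 1.555 and Z < −0.524, with correlation √(33/99) between the two looks. Numerical integration with binding futility gives:

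| True effect (log10) | Success at interim | Success at final | Total | Plan states |
|---|---|---|---|---|
| 0 | 6.0% | 3.98% | 9.98% | below 10% |
| 0.5 | 42.0% | 38.4% | 80.4% | 80% |
| 0.6 | 52.8% | 37.6% | 90.4% | over 90% |

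The stated figures are correct on their own inputs.

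**2. Assumed inputs.** The protocol gives neither the share p of patients on a background antiviral at randomisation nor the antiviral's effect g on viral load change. I take p from 20% to 50% and g from 0.3 to 0.5 log10, with g = 1.0 as an upper case. That upper case is twice the effect the trial is designed to detect.

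**3. Chance imbalance at the interim.** The SD of the difference in proportions is √(2p(1−p)/33).
- p = 30%: √(0.42/33) = 0.113; 95% range ±1.96 × 0.113 = ±22 points.
- p = 50%: √(0.50/33) = 0.123; 95% range ±24 points.

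The shift in the estimate is imbalance × g. At the edge of those ranges it is 0.22 × 0.5 = 0.11 to 0.24 × 0.5 = 0.12 log10. At g = 1.0 it is 0.22 to 0.24 log10. Adjustment for baseline viral load may already absorb part of this.

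**4. Scale.** The interim standard error is 1.5 × √(2/33) = 0.37 log10. The efficacy boundary needs an observed benefit of 1.555 × 0.37 = 0.57 log10. A shift of 0.11 to 0.12 is about 0.3 standard errors (0.115/0.37). At g = 1.0 the shift is about 0.6 standard errors (0.23/0.37).

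**5. Precision.** The share of outcome variance explained by a yes/no covariate is p(1−p)g²/1.5².

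| p | g = 0.3 | g = 0.5 | g = 1.0 |
|---|---|---|---|
| 20% | 0.6% | 1.8% | 7.1% |
| 50% | 1.0% | 2.8% | 11.1% |

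The standard error shrinks by the factor √(1 − share). At 2.8% that is √0.972 = 0.986, about 1.4% narrower. At 11.1% it is √0.889 = 0.943, about 5.7% narrower.

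**The case against.** Phase II is an add-on trial: placebo plus standard of care, double-blind, analysed by intention-to-treat. The effect on top of real-world care is a legitimate target. Randomisation balances baseline antiviral use in expectation, and baseline viral load is in the model. The scatter from chance imbalance already sits inside the SD of 1.5 and the stated error rates. On Section 2.1's account the named antivirals are recommended in non-severe disease, which points mainly to Grade 4, so actual use could be low. All of this stands, and it is why the point is modest. It does not remove the case for a nearly free covariate: error rates that hold on average do not correct an imbalance that has occurred.

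Three stronger readings are tempting, and the documents do not support them.
- **Background antivirals bias the comparison.** Leaving out a baseline covariate does not bias a 1:1 randomised contrast. A smaller effect in patients already on an antiviral is part of the true add-on effect.
- **The trial loses a calculable amount of power, which adjustment would restore.** Any such figure needs the share of users and the favipiravir effect that remains in them, and the protocol gives neither. A covariate does not undo dilution in any case.
- **An antiviral started before Day 3 needs its own primary-endpoint analysis, with later swabs set to missing.** Bias would require unequal starts between arms within about two days under blinding. Intention-to-treat implies using the data as observed, and further handling can sit in the SAP. Setting swabs to missing would assume missingness at random in patients whose start may depend on their course.

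**Conclusion.** The point holds as a limited improvement to the primary model. The protocol permits active antivirals on a virological endpoint and records their use, but fixes a primary model and an allocation method that ignore it. No stated figure is wrong, and the randomised comparison is valid.

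The cost has three parts: an uncorrected chance imbalance, worth about 0.3 standard errors at the interim in an unlucky draw (30-50% use, 0.5 log10 antiviral effect); about 0.6-3% of outcome variance left unexplained (0.3-0.5 log10, 20-50% use), rising to about 11% only at 1.0 log10 and 50% use; and a null or futility result that is harder to read. The two numerical sizes rest on assumed usage and effects. If few enrolled patients are on an antiviral, they shrink towards nothing.

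**What to change.** In Section 10.3.2, add one baseline covariate to the primary model: SARS-CoV-2 antiviral or antibody treatment given or ongoing at randomisation (yes/no). Derive it from the medication record in Section 6.10, using only entries that start before randomisation, so that it is a true baseline variable. Report the Day 3 treatment effect descriptively with and without background antiviral, at the final analysis and to the DMEC at the 66-patient look. Keep the intention-to-treat analysis, with data used as observed, as primary.

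The cost is a sentence or two of protocol text, one derived variable and one extra model parameter. It needs no further patients or visits and no change to permitted care. The descriptive split will be imprecise, especially at 33 per arm. It should be read as an aid to interpretation and not as a test.
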